### Inertial sensor based motion and gait analyses

Movement analysis by body-fixed inertial sensors containing accelerometers and gyroscopes enables the objective assessment of the translational and angular movements of body segments outside a gait laboratory [44,45]. We used a single 3D inertial sensor (41x63x24mm; 39g; Microstrain Inertia Link) containing accelerometers (±5g) and gyroscopes (±300°/s) along the three orthogonal axes in frontal, sagittal and transverse plane and positioned centrally between both posterior superior iliac spines to measure trunk movements near the center of gravity. Based on the 3D linear accelerations, angular rates and angular positions put out by the sensor and send wirelessly to a PC at a 100Hz sampling frequency via a Bluetooth link, analysis algorithms calculate motion parameters such as step frequency, step asymmetry or trunk sway.

The inertial sensor was used to derive motion parameters from a battery of movement tasks which are clinically feasible to perform during a routine outpatient visit and which challenge the patient’s functional capacity in different ways: 1) locomotion (walking); 2) transfers (sit-stand-sit, get up and go); 3) rising and descending (step test) and 4) balance tests (single leg stance). The walk test [46] and the step-test are repeated twice and the sit-stand-sit test is repeated three times to derive representative mean values or study possible effects of fatigue or warming up.

### Data collection

Information on body mass index, diagnosis, side of surgery, type of surgery and surgical approach is extracted from participants’ medical records.

### Data recording

All data is entered into a password-protected database by research nurses or study administrators. The study is overseen by an independent Steering Committee which meets every 6 months to discuss the progress of the study. Data monitoring, which involves double data entry and quality checks, is conducted every 3-months. All data will be cleaned before data analysis is performed. Any inconsistencies will be collegially discussed by an internal board of researchers involved in the data collection.

### Sample size

This study will involve exploratory analysis to compare different measures to assess function after TJR. Therefore, no formal sample size calculation was performed, although we aimed to recruit a sufficient number of patients to allow meaningful data analysis. We approached all patients listed for surgery with participating surgeons between February 2010 and November 2011. Previous longitudinal studies comparing measures of function in an orthopaedic population have included between 30 and 200 patients [22,47-54]. Recruitment for this study is complete and 133 knee replacement patients and 130 hip replacement patients have been recruited, making this one of the largest longitudinal studies to compare measures of function in TJR patients. The 133 patients listed for a knee surgery are planned to receive a primary total knee replacement (n=51), a revision total knee replacement (n=45), a unicompartmental knee replacement (n=32) or a patello-femoral replacement (n=5). The patients listed for a hip surgery are planned to receive a primary total hip replacement (n=78), revision total hip replacement (n=44) or a hip resurfacing (n=8).

### Data analysis

This section is an overall presentation of the quantitative and qualitative analysis plan and does not intend to provide a detailed account of all forthcoming analysis. Nested analyses using sub-groups of patients are also planned.

#### Quantitative analysis

Participation rates will be compared by age, gender and postcode with Poisson modified regression[55]. Descriptive statistics alongside measures of precision (95% Confidence Intervals) will be used to present the measures at each assessment time. The first investigations will focus on the pre-operative period. Receiver Operating Characteristic curve, correlation analyses or generalized linear models (GLM)[56] will be considered to study the relations between measures aiming to describe the same domain (I, A or P) or between performance test, self-assessed and clinically-administrated measures. We will also study how the various measures of A correlate to P (measured with the Ab-IAP).

For each self-reported and clinician-administered assessment of function, internal responsiveness will be investigated by dichotomising patients into those that do and do not improve as a result of surgery using established methods such as the “OMERACT-OARSI responder criteria” or the “Minimum Important Difference” [57,58]. External responsiveness will be explored by calculating the minimum clinically important difference (MCID) for each measure, using the Self-Administered Patient Satisfaction Scale as the clinical anchor to derive MCIDs.

The role of patients’ pre-operative characteristics (Table 2) on responsiveness will be studied with GLMs. The distribution of the pre-operative measures (skewness, peakedness and percentiles) will be used to derive patient classifications by levels of I, A or P. Patient profile will also be adjusted for in the multivariate analyses. Concordance in responsiveness between measures will be studied. These comparisons will be re-conducted within each pre-operative I,A or P patient profiles. Adjusted and non adjusted GLMs will be used to study the association with responsiveness and the outcomes of performance tests for measures specific to the A domain.

The longitudinal aspect of the data collection will allow the study of the change in the measures between the pre-operative period and two time points after surgery. Generalized linear mixed or marginal models[59] will be used to study the patients’ trajectories and investigate the impact of pre-operative and time-dependant patients characteristics. Particular attention will be paid to the distributions of the raw scores of each measure and appropriate transformation or categorisation will be conducted. Tests such as the Log-likelihood ratio test or the Wald test will be used to identify statistically significant effects or interactions (*P*<0.05). Missingness will be investigated and if necessary Multiple Imputation by Chained approach will be considered and estimates combined with Rubin’s rules. The analyses will be conducted with Stata 11.2.

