### Assessment times

Participants attend a mutually convenient research appointment, lasting approximately one hour, at the AOC. Appointments are scheduled before surgery and then at 3-months and 1-year after surgery. Assessments are conducted at 3-months post-operative to coincide with the standard clinical review, by which time most patients have experienced a large improvement in pain and function [26]. Assessments are also conducted at 1-year post-operative as outcomes can continue to improve up until this time point [26]. The inclusion of two post-operative assessments also allows exploration of outcome trajectories and comparison of rates of improvement between different outcome domains (e.g. pain, function, participation).

At the initial pre-operative appointment eligibility was confirmed, informed written consent was obtained and a questionnaire was given to participants to return by post before their operation. For the post-operative assessments, a questionnaire is sent out prior to the research appointment. At each time point, participants undergo a clinical assessment. These assessments are conducted by trained research nurses who follow standard operating procedures to ensure consistency and standardisation in data collection and who were assessed for competency in the examination procedures by a senior research nurse and orthopaedic surgeon. Risk assessments of the functional tests were undertaken and safe operating procedures specified. The data collected during the assessments are recorded by the research nurses on standardised proformas.

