Participants also complete a number of other questionnaires to assess factors that have been found to influence outcomes after TJR (Table 2). At each assessment time, participants complete the Hospital Anxiety and Depression Scale [36] and the WOMAC Pain and Stiffness Subscales [32]. Participants are also asked to rate how disabled they perceive themselves because of their joint problems and why, and to list three things that they are hoping for from their TJR. Pre-operatively, medical co-morbidities are recorded using the Functional Co-morbidity Index [37] and information is collected about socioeconomic status (marital status, living arrangements, educational attainment, employment status), joints affected by arthritis, and previous surgery on other joints. In the 1-year post-operative questionnaire, satisfaction with the outcome of surgery is assessed using the Self-Administered Patient Satisfaction Scale for Primary Hip and Knee Arthroplasty [38].

**Table 2 T2:** Summary of measures used to assess factors influencing function

	**Dimensions**	**Mode of completion**	**Scoring**	**Assessment times**		
				**Pre-op**	**3-month**	**1-year**
WOMAC pain subscale	Joint pain	Patient	0-20	✓	✓	✓
WOMAC stiffness subscale	Joint stiffness	Patient	0-8	✓	✓	✓
Hospital and Anxiety Depression Scale	Depression, anxiety	Patient	0-21	✓	✓	✓
SF-12 Mental Component Score	Mental health	Patient	0-100	✓	✓	✓
Perceived level of disability	Function	Patient	0-10	✓	✓	✓
3 things hoping for from surgery	Expectations	Patient	Categorical	✓	✓	✓
Functional Co-morbidities Index	Co-morbidities	Patient	0-18	✓		
Arthritis and surgery in other joints	Co-morbidities	Patient	By joint/count	✓		
Socioeconomic status	Socioeconomic	Patient	Categorical	✓		
Self-Administered Patient Satisfaction Scale	Satisfaction	Patient	0-100			✓

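### External responsiveness is reported as an MCID per measure, which does not show which measure better separates responders from non-responders

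*Protocol article*

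**What the plan says.** The Background section of the protocol article states the aim of comparing commonly used measures of function on their properties and responsiveness. It explains responsiveness as being able to tell responders to joint replacement from non-responders.

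The Quantitative analysis section gives the method: "External responsiveness will be explored by calculating the minimum clinically important difference (MCID) for each measure". The same sentence then fixes the anchor for these thresholds: "using the Self-Administered Patient Satisfaction Scale as the clinical anchor to derive MCIDs". No other metric or anchor is named for external responsiveness. Internal responsiveness is to be studied by splitting patients into improved and not improved by established criteria, and concordance in responsiveness between measures is to be examined. ROC curves appear in the same section, but only for relations between measures, directly after the sentence on the pre-operative period. They are not linked to change against the anchor.

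On timing, "Appointments are scheduled before surgery and then at 3-months and 1-year after surgery". The anchor is collected at the last visit only: "In the 1-year post-operative questionnaire, satisfaction with the outcome of surgery is assessed using the Self-Administered Patient Satisfaction Scale". Table 2 agrees, with a tick in the 1-year column alone. Participants also rate "how disabled they perceive themselves because of their joint problems" on a 0-10 scale, and Table 2 shows this at all three visits.

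**The concern.** The aim is comparative: which instrument better identifies responders. The planned result is a set of cut-points. A cut-point says how much change on a given scale goes with being satisfied. It does not say how reliably change on that scale separates satisfied from dissatisfied patients. Two instruments can share an MCID and differ widely in discrimination, or discriminate equally and have different MCIDs because their score ranges differ. If MCIDs are the only external-responsiveness output, the study could finish with a table of thresholds and no answer to its comparison question. Nor does any other index named for responsiveness rank the instruments, since internal responsiveness is also a responder split.

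**Working it through.** The article gives no MCID, AUC or responsiveness figure, so there is nothing of its own to reproduce except recruitment: 51+45+32+5 = 133 knee, 78+44+8 = 130 hip, total 263. These agree with the stated counts.

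**1. Units (Table 1).** WOMAC function 0-68; Ab-IAP 9-45, 17-85 and 9-45; SF-12 PCS 0-100; MYMOP2 0-6; AKSS and HHS 0-100. MCIDs on these scales are not on a common footing.

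**2. Does an MCID track discrimination?** I used an illustrative simulation of 200,000 patients. Every input is an assumption: baseline function SD 1; mean change 1.5 SD; residual SD of change 0.9; slope of change on baseline -0.4; an anchor equal to true change plus noise of SD 0.7; 15% not satisfied. Measures A and C have 12 points per SD (0-68 scale). Measure B has 12 x 100/68 = 17.6 (0-100 scale). Measurement-error SD is 0.3 for A and B and 1.0 for C.

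| Measure | MCID, ROC cut-off | MCID, mean difference | AUC of change | SRM |
|---|---|---|---|---|
| A, 0-68 | 12.5 | 17.5 | 0.88 | 1.40 |
| B, 0-100, same quality | 17.8 | 25.8 | 0.88 | 1.40 |
| C, 0-68, noisy | 11.7 | 17.7 | 0.74 | 0.87 |

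The standardised response means (SRM) can be checked by hand. The variance of true change is 0.9² + 0.4² = 0.97. For A, 1.5/√(0.97 + 2 x 0.09) = 1.40. For C, 1.5/√(0.97 + 2 x 1.0) = 0.87.

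A and B discriminate equally but have different MCIDs. A and C have nearly the same MCID but different discrimination. This holds for either way of deriving the MCID. It also holds if the anchor follows the 1-year state instead of change: ROC MCIDs 13.9, 22.9 and 15.1; AUCs 0.71, 0.71 and 0.63.

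**3. Does concordance fill the gap?** Concordance between responder classifications is free of units, but it measures agreement. If two instruments disagree on a patient, it does not say which one was right against the anchor.

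**4. Timing.** The anchor is given once, at 1 year, so there is no concurrent anchor value for change to 3 months. An MCID from this anchor is a 1-year quantity.

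**5. Is the anchor related to change?** With equal variances, and if satisfaction acts only through the 1-year score, corr(satisfaction, change) = r_s(1 - r_p)/√(2 - 2r_p), where r_s is its correlation with the 1-year score and r_p the pre-post correlation. Assumed r_s of 0.5-0.7 and r_p of 0.3-0.5 give 0.25 (0.5, 0.5), 0.33 (0.6, 0.4) and 0.41 (0.7, 0.3). On the 3 x 3 grid, 6 of 9 values reach 0.30, taken here as an illustrative acceptance level. The anchor may therefore be adequate, but the article states no check of it.

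**6. Numbers behind a cut-point.** At an assumed 10-20% not satisfied and no attrition, that group is 26-53 of 263, or about 13-27 within hip or knee alone, where HHS and AKSS must be anchored.

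**The case against.** The strongest reply is that an MCID does classify patients as responders or not, which is what the stated aim asks for. The cross-instrument comparison is assigned to concordance, and nowhere does the article say raw MCIDs will be ranked. An MCID found by ROC would also give an AUC in passing. The study is exploratory, and the article says it does not detail every analysis. What stands is that the plan is not internally contradictory and that the matter is not urgent. What does not stand is that the aim is therefore met. Classification by a threshold is not evidence of how well the threshold works, and the MCID itself is the stated external-responsiveness result.

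A reader might infer four stronger points. The documents do not support them.

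- **That the plan fails at 3 months.** No section promises an MCID at 3 months. Change to both visits is assigned to mixed or marginal models.
- **That satisfaction is invalid because it rates the end state.** The article describes it only as satisfaction with the outcome of surgery and does not give the items. The 0.25-0.41 range builds in the assumption that satisfaction acts only through the 1-year score. In the simulation an end-state anchor moved the ROC MCID from 20.0 (worst baseline tertile) to 4.6 (best), but even a true change anchor gave 15.2 to 9.1.
- **That the MCIDs will be too imprecise.** With 15% not satisfied and a 0.8 SD separation (both assumed), a Youden cut-off at n = 131 has a simulated 95% range of about -0.1 to 1.6 SD. The plan does not name that estimator. Under the same assumptions the midpoint of the group means gives 0.56 to 1.03 SD.
- **That the scale is unsuitable for revision patients.** They are 45 + 44 = 89 of 263 (34%), but the point rests only on the word primary in the scale's title.

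**Conclusion.** The concern holds as a mismatch between metric and aim. The article fixes external responsiveness as an MCID, and an MCID cannot show which instrument better separates responders from non-responders. Because the metric is stated, this is not detail left to a fuller plan. In the simulation the MCID barely moved (12.5 against 11.7) while the AUC fell from 0.88 to 0.74. Those sizes depend on assumed inputs. That a cut-point in native units is not a measure of discrimination does not depend on them. The end-state and imprecision figures are illustrative only. This is a recommended improvement to an exploratory analysis, not a must-fix.

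**What to change.** In the Quantitative analysis section:

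- For each measure, report the AUC and the correlation of its 1-year change score against the satisfaction anchor, with 95% CIs. State in advance the satisfaction cut used for the AUC; the correlation needs none. Make these the external-responsiveness result.
- Compare instruments by paired bootstrap CIs for differences in the same patients. HHS and AKSS can be paired with other measures only within hip or knee.
- Keep the MCID as an interpretation aid, state that it applies at 1 year, and print the anchor-change correlation beside it.
- As a sensitivity analysis, repeat at 3 months and 1 year with change in the 0-10 perceived-disability rating as anchor. Note that Table 2 lists this item under function and that it is self-report, so it may favour questionnaires over clinician-administered scores and performance tests. It should supplement the satisfaction anchor, not replace it.

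The cost is wording and analysis time; all the data are already being collected. With perhaps 13-27 dissatisfied patients per joint, some intervals will be wide, and showing that is part of the result.

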### Selection of outcome measures

Table 1 provides a summary of the functional assessment measures used in this study. The Table also provides an overview of the ICF domains included within each functional assessment measure, with classification of self-completed PROMs and clinician-administered measures based on the results of an expert consensus study by Pollard and colleagues [15]. There are a number of other measures that could have also been included in this study such as the Oxford hip and knee scores [27,28], Hospital for Special Surgery Score [29], Knee injury and Osteoarthritis Outcome Score [30] and Nottingham Health Profile [31]. However, to avoid participation burden and fatigue only a selection of measures was chosen, which are outlined below.

**Table 1 T1:** Summary of measures used to assess function pre-operatively and at 3-months and 12-months post-operatively

	**ICF domains assessed**			**Mode of completion**	**Scoring**
	**I**	**A**	**P**		

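### The responder models name only a categorised I/A/P profile as adjustment for pre-operative function; each measure's own pre-operative score should be added as a continuous covariate

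*Protocol article*

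**What the plan says.** All of this stands in the protocol article.

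- **Outcome.** For each self-reported and clinician-administered measure, responder status is formed by "dichotomising patients into those that do and do not improve as a result of surgery", using the OMERACT-OARSI criteria or a Minimum Important Difference (Quantitative analysis).
- **Predictors.** "The role of patients’ pre-operative characteristics (Table 2) on responsiveness will be studied with GLMs".
- **Adjustment.** Skewness, peakedness and percentiles of the pre-operative measures "will be used to derive patient classifications by levels of I, A or P", and then "Patient profile will also be adjusted for in the multivariate analyses".
- **What is available.** The function measures are all taken before surgery; the Table 1 caption reads "Summary of measures used to assess function pre-operatively and at 3-months and 12-months post-operatively". Table 2 contains none of these function scores. It does contain pre-operative WOMAC pain and stiffness, anxiety and depression, the SF-12 mental score and a 0–10 rating of perceived disability.
- **Status.** The study is exploratory: "Therefore, no formal sample size calculation was performed". The opening of Data analysis describes the section as an overview.

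**The concern.** Whether a patient passes a change threshold depends strongly on where the patient starts. A poor starting score leaves room to improve; a score near the best end may make the threshold unreachable. Several Table 2 factors, such as pain, depression and perceived disability, are likely to go with worse starting function. A class holds starting level constant only between classes. Inside a class, patients still differ in starting level, and a correlated predictor picks up that difference.

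Two errors can follow. A factor that merely marks a worse start may appear to raise the chance of response. A factor that truly worsens the result may look harmless, because its effect is offset by the extra room to improve. Both bear on the question these models address: which patients improve.

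**Working it through.** **Inputs from the article.** N = 263: "133 knee replacement patients and 130 hip replacement patients have been recruited", and the subgroups agree (51+45+32+5 = 133; 78+44+8 = 130). Significance level 0.05, taken as two-sided. There is no power or event figure to reproduce.

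**Assumed inputs, because the article gives none.** Baseline B is standardised, high = worse. Predictor X correlates r with B (0.3–0.7). Follow-up F correlates 0.4 with B (varied 0.2–0.6). Another instrument C correlates 0.7 with B. Mean improvement is 1.4 SD and a responder improves by at least 0.8 SD (varied to 0.5), giving about 71% responders in the main scenario.

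**Step 1: why a class is not enough (algebra, r = 0.5).** Change = B − F + 1.4, so each SD of worse baseline brings 1 − 0.4 = 0.6 SD more improvement. Suppose X has no effect given B. If the class explains a share k of the variance of B, the spurious slope of change on X is about

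0.6 × r(1 − k) / (1 − r²k).

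- No adjustment, k = 0: 0.6 × 0.5 = 0.30.
- Own-score tertiles: the outer-tertile mean of a normal score is 3φ(0.431) = 1.091, so k = (2/3) × 1.091² = 0.793. Slope = 0.6 × 0.103 / 0.802 = 0.08.
- Tertiles of the other instrument: k = 0.7² × 0.793 = 0.389. Slope = 0.6 × 0.306 / 0.903 = 0.20.
- Continuous own score: 0.

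**Step 2: simulated logistic models, X null given B, n = 263, 1,500 replicates.** Share significant (odds ratio per SD of X):

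| Adjustment | r = 0.3 | r = 0.5 | r = 0.7 |
|---|---|---|---|
| 2 own-score classes | 11.7% (1.13) | 25.5% (1.24) | 55.3% (1.46) |
| 3 own-score classes | 7.5% (1.07) | 11.4% (1.13) | 24.1% (1.27) |
| 4 own-score classes | 6.1% (1.05) | 7.9% (1.09) | 13.8% (1.18) |
| 3 classes, other score | 24.5% (1.21) | 59.7% (1.40) | 91.1% (1.73) |
| Continuous own score | 5.8% (1.01) | 5.0% (1.00) | 5.0% (1.01) |

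At r = 0.5, changing the baseline–follow-up correlation to 0.2 or 0.6 moves the own-tertile figure to 12.7% or 8.0%. At n = 130 (one joint), own-score tertiles give 5.7–13.8% and other-score tertiles 14.7–62.0%. Monte Carlo error is at most about 1.3 points.

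**Step 3: masking.** Let X truly worsen follow-up by 0.2 SD per SD (r = 0.5, n = 263). Power is 58.4% with the continuous own score, 33.8% with four own-score classes, 24.6% with three, and 6.3% with tertiles of another score. The algebra agrees. Here F = 0.3B + 0.2X + error, so the multiplier is 1 − 0.3 = 0.7. The net slope with the other-score class is −0.2 + 0.7 × 0.306 / 0.903 = +0.04, so the harm is cancelled. A second scenario (r = 0.4, other-score correlation 0.75, mean improvement 1.2 SD, threshold 0.5 SD) gives power of 60% (continuous), 35% (own tertiles) and 9% (other-score class).

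**Step 4: other Table 2 covariates in the model.** Pain, perceived disability and a psychological factor were entered together, all null given baseline (correlations with baseline 0.5–0.7, 0.5–0.6 and 0.3–0.4; other-score correlation 0.75; 800 replicates; n = 263). With another score's tertiles, false positives were 41–63%, 34–44% and 12–18% respectively. With own-score tertiles they were 5–18%, and with the continuous own score 3.5–6%.

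**The case against.** The strongest reply is that much of the worry is read into silence. A reader might infer that the class is the sole baseline term and that the continuous score is left out. The article does not say so: the profile is adjusted for in addition to other covariates, nothing excludes the own score, and the section is declared an overview. A reader might also infer that the classes are coarse, or taken from a different instrument. Neither is stated. Only the Ab-IAP is rated as mainly covering all three domains in Table 1, and the Harris Hip Score and American Knee Society Score are each used in one joint group. A class from another instrument is therefore a realistic possibility for some measures, but no more than that. All of this stands, and the largest figures above must not be read as the plan's expected error rate.

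Second, the Table 2 covariates carry some baseline severity, so a single-predictor simulation overstates the bias. This stands in part. Adding two severity covariates to a scenario with r = 0.4 cut the other-instrument rate from 33% to 16–21% at n = 263, and own-score tertiles then gave 6–8%. Step 4 shows less relief for pain and perceived disability, which are themselves predictors under study.

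Third, conditioning on baseline changes the estimand in an observational cohort. That is true in general, but the plan already conditions on starting level through the profile; the question is only how well.

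Fourth, the mixed or marginal models also examine predictors. They are a separate analysis and do not correct the responder models.

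**Conclusion.** The point holds in a limited form. For an outcome that depends on change, the article names a categorised profile as its adjustment for pre-operative function, and a better form is available from data already collected. Predictor effects can be confounded by starting level; the documents do not show that they will be.

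The size rests on assumed correlations and on the unstated number and source of the classes. Own-score tertiles cost a modest excess of false positives in typical scenarios and, for a 0.2 SD effect, lower power from about 60% to 25–35%. Four own-score classes do less harm. A class from another instrument does considerably more. The continuous own score stays near the nominal level throughout. In an exploratory study this is worth correcting before analysis, but it does not undermine the design.

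**What to change.** State that each GLM of responder status on a measure includes that measure's own pre-operative score as a continuous covariate, linear or as a restricted cubic spline with three knots, alongside the I/A/P profile. Keep the profile for the planned within-profile comparisons. State also how many classes there are and which measure defines them.

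The cost is a wording change and one or two degrees of freedom per model. No new data are needed, and the Discussion places the analysis in 2013, after data collection. The downside is slight over-correction if the baseline score is measured with error: at an assumed reliability of 0.8–0.9, the odds ratio for a null predictor was 0.95–0.97 instead of 1.00, with false positives of 5–6%.
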